#### Completion rate of follow-up measures

Completion rates will be assessed through the number of participants providing complete data for the 3-month follow-up measures (from consent date), 6-month follow-up measures and telephone interviews. The telephone interviews will also be used to ask participants how to optimise the follow-up response rate and maintain contact. Together, this information will be used to estimate the expected response rate and inform the design of a definitive RCT.

### Secondary feasibility measures

#### App usage

App usage during counselling sessions will be assessed through audio recordings to determine how various features are discussed between participants and counsellors. The discussion of clients’ app usage to monitor behaviours, thoughts, emotions and therapeutic exercises is an essential component of using feedback in therapy and in integrating the well-being app with counselling. Therefore, analysis of app discussion aims to identify dominant app features, inform potential moderators of therapeutic outcomes in the definitive trial and evaluate intervention fidelity (discussed below). Analysis of app discussion will also consider the added gain of using the purchased app version over the free version, by categorising discussion by features associated with either version of the app. A final exploration of app discussion will match app features with context-specific benefits, client characteristics and potential risk.

Participant app usage between counselling sessions will be addressed in follow-up telephone interviews to inform the acceptability of using a well-being app alongside counselling, and exploring the timeframe for how long the well-being app was useful for participants. Participant usage of the app overtime will also be explored through app data (e.g. log in times, duration of time spent using each feature), but this will be dependent on the availability of data and on participant consent to access app data.

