After the routine clinical assessment, participants will attend a one-to-one research interview (approximately 20 min) to provide written informed consent and determine eligibility before potentially joining the trial. During the research interview all participants will be informed about both treatment conditions and will be asked their preference (See later section on “Treatment preference”). The preference, as well as associated reasons for preference, will be recorded in the recruitment checklist information. Irrespective of the condition, participants will not be asked to cease using any existing well-being apps, but their use will be noted in the recruitment session and explored in the exit telephone interviews. Whilst the use of existing apps may pose risk of contamination, the enhanced intervention relies on the integration of app activity within counselling and participants in the control condition will not receive guided advice on the well-being apps they may use. In addition, group differences in outcome measures can be compared before/after participants are removed for using additional well-being apps. Combined, this information will be used to inform the recruitment rate, randomisation procedure, allocation procedure and blinding for a fully powered RCT.

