### Counselling interventions

All participants will receive an active treatment in line with standard practice and will not be disadvantaged by participating in the trial. Participants will have access to the standard level of care at Sheffield UCS, which includes a wait period of typically 3–5 working days for the initial clinical assessment and 8–10 days between ongoing therapy sessions. This wait period varies throughout the year but the service agreement offers first contact within 10 days, and this is typically shorter than the NHS waiting times.

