#### Treatment satisfaction

Participant treatment satisfaction will be assessed with the 8-item Client Satisfaction Questionnaire (CSQ-8) [27], which will be emailed to participants the day after their last counselling session. CSQ-8 items refer to a client’s overall service experience and are rated on a 4-point Likert scale (1 = “quite dissatisfied”; 5 = “very satisfied”) whereby higher scores indicate greater satisfaction. Many counselling services report on client satisfaction to allow comparison to other services and to ensure that services respond to client feedback. Capturing client satisfaction will also allow comparisons between treatment conditions to explore whether the enhanced intervention had a positive or negative impact on a participant’s service experience. A sub-sample of participants’ service experiences will also be explored through telephone interviews after counselling completion. Finally, counsellor satisfaction in the delivery of the enhanced intervention will be assessed through a focus group once all participants have completed counselling.

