Approximately 40 h of therapy is anticipated to be recorded, transcribed and analysed. The conservative estimation for recordings considers several factors including the following: (1) although participants will be offered ~6 counselling sessions, the services’ median number of attended sessions is 2 and 4; (2) participants (and therapists) may decide not to record a session where the participant is particularly distressed; (3) trial budget available to fund transcription; and (4) feasibility trials are not required to be powered to detect significant effects but to provide sufficient preliminary indicators. Whilst data from the therapy recordings is qualitative in nature, they will be analysed with “quantitative” content analysis [29] whereby sessions will be scored to indicate intervention fidelity and implementation success. These scores will be achieved by using a checklist developed from the training materials to rate the extent to which therapists delivered the new intervention (see “Intervention fidelity” section). A random sample of 15 therapy hours will be assessed by an independent researcher, blind to the aims of the study, to permit analysis of inter-rater reliability.

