#### Qualitative analysis

A number of feasibility factors will be explored qualitatively through counsellor clinical notes, a therapist focus group, and participant exit interviews; to explore the feasibility, acceptability and potential implications of supplementing counselling with a well-being app. The clinical notes will be extracted from the sessional notes taken as part of routine practice, except counsellors will additionally reflect on their experience of integrating the app and how the app fitted with their client/therapy style. These experiences will be explored in more detail at the end of the trial through a one-off therapist focus group. The participant exit interviews will take place once clients finish counselling and thus may occur throughout the trial depending on how early clients were recruited and how many counselling sessions they agreed to have with their therapist. The aims of the exit interviews are threefold: (1) to capture clients’ experiences of the new intervention (and indirectly inform intervention fidelity); (2) to distinguish areas of improvement for research design; and (3) to identify whether counselling contributed to their ability to cope at university. Data from the client interviews, therapist focus group and clinical notes will be analysed flexibly and explorative with thematic analysis to allow themes to emerge from the data and to allow comparisons across different data sources [30]. By exploring themes across various data sources, the current study aimed to provide a rounded and comprehensive account for the following: (1) how well the app was integrated into counselling (according to clients, therapists and researchers) and (2) the potential risks/benefits of integrating an app with counselling, if implementation is successful. Qualitative data will be analysed with NVivo (version 11).

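### How long the app stays useful is asked only in an interview tied to the end of counselling, so anyone still using it then can answer only for the time so far

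*Protocol article*

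**What the plan says.** All references are to the protocol article.

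- **App usage** (secondary feasibility measures) names the instrument: "Participant app usage between counselling sessions will be addressed in follow-up telephone interviews". The same sentence gives two purposes: to judge whether use of the app alongside counselling is acceptable, and "exploring the timeframe for how long the well-being app was useful for participants".
- **Qualitative analysis** gives the timing: "The participant exit interviews will take place once clients finish counselling and thus may occur throughout the trial". The section on treatment satisfaction agrees: a sub-sample's experiences "will also be explored through telephone interviews after counselling completion". The allocation section says that use of other well-being apps will be "explored in the exit telephone interviews". The exit interview and the telephone interview therefore appear to be the same contact.
- **Completion rate of follow-up measures** lists the telephone interviews as an item separate from the 3- and 6-month measures. Table 1 has only PHQ-9, GAD-7 and CD-RISC 10 at those two contacts, and no item on the app.
- **App usage** adds one further source on use over time, the app's own data, but "this will be dependent on the availability of data and on participant consent to access app data".

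**The concern.** A question about how long something remained useful can be answered in full only by people for whom it has stopped being useful. Anyone still benefiting at the exit interview can give only the time elapsed so far. That time is set by the number and spacing of their counselling sessions, so participants with longer counselling have more opportunity to report longer usefulness, whatever the app itself does. Those who finish early are cut off soonest.

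At stake is one of the things the feasibility study says it will explore, and one that would help in designing the later trials. The background and discussion stress support that fits around the academic calendar and periods away from campus. Whether the app remains useful beyond the last session bears on that, although the article does not name it as an aim. No primary feasibility output depends on it.

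**Working it through.** The article states no figure on this point, so there is none to reproduce. The check is how far into app use an end-of-counselling interview would fall.

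**Inputs**

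- Spacing: the section on counselling interventions gives typically "8–10 days between ongoing therapy sessions".
- Sessions attended: the quantitative analysis section gives the service's "median number of attended sessions is 2 and 4". The phrase is unclear, so both values are used.
- Maximum in the trial: 6 sessions, with frequency agreed individually, across a 6-month period (abstract; TAU and enhanced-intervention sections).
- Last planned contact: 6 months after consent, taken as 183 days.

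**Formula**

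Days from first to last session = (sessions − 1) × gap.

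| Sessions | Calculation | Days | Share of 183 days |
|---|---|---|---|
| 2 | 1 × 8 to 1 × 10 | 8–10 | 4–5% |
| 4 | 3 × 8 to 3 × 10 | 24–30 | 13–16% |
| 6 | 5 × 8 to 5 × 10 | 40–50 | 22–27% |

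The range is therefore about 1 week (8/7 = 1.1) to 7 weeks (50/7 = 7.1).

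**Sensitivity 1: earlier start of app use.** The article does not say when the app is issued. If it is issued one gap before session 1, add 8–10 days. This gives 16–20, 32–40 and 48–60 days for 2, 4 and 6 sessions, or 9–11%, 17–22% and 26–33% of 183 days.

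**Sensitivity 2: the nominal end of treatment.** The PHQ-9/GAD-7 and CD-RISC 10 sections describe the 3-month contact as following the end of treatment. If counselling really ends then, the period is about 91 days, or 91/183 = 50% of the 6 months. Six sessions would need a gap of 91/5 = 18.2 days to take that long, about twice the typical spacing.

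**Sensitivity 3: the full window.** Six sessions spanning 6 months would need a gap of 183/5 = 36.6 days. The window permits this, but it is far from the typical spacing.

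**Result.** The period that an exit interview can cover runs from about 1–7 weeks at typical spacing to about 3 months at the nominal end of treatment. It is longer with wide spacing or a delayed interview. In each case the length of counselling and the interview date set the limit, and the article describes no later contact at which the question is asked again.

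**The case against.** Four points on the other side have force.

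- **The sentence is framed around use alongside counselling.** It opens with app use between sessions, so the timeframe may mean how long the app helped while counselling lasted. An exit interview is a natural place to ask that. The wording leaves both readings open. A reader might infer that persistence after counselling is a declared aim, but the document does not say so. Nor does it make the annual app subscription an observation period; that is simply what was bought.
- **The interview date is not fixed.** No lag after the last session is given, and the interviews are also called follow-up interviews. A reader might infer that a two-session client is interviewed within a week or two. That assumes typical service spacing and no delay, and neither is guaranteed. Spacing varies through the year and is agreed individually, the medians are for the service as a whole, and the article elsewhere places the end of treatment at 3 months.
- **No duration statistic is planned.** Interviews are analysed thematically. A reader might infer that a biased estimate of duration will be reported, or that a time-to-event analysis is needed. Neither follows. A statement that someone stopped in the second week, or still uses the app, is a usable qualitative answer, and those who stopped before the interview answer completely.
- **Other sources exist.** App logs could run past the end of counselling, and session recordings and counsellor notes bear on usefulness during it.

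These points reduce the size of the problem but do not remove it. Participants still finding the app useful at exit remain incompletely observed, and no later question to them is described. The logs are conditional and show use, not perceived usefulness.

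**Conclusion.** The point holds as a minor one. It is a limit on what the chosen contact can show, not a contradiction or an invalid analysis. For participants still benefiting at exit, the answer on duration is a lower limit governed by the length of their counselling. That limit is about 1–7 weeks at typical spacing with 2 to 6 sessions, about 3 months if counselling ends at the nominal 3-month contact, and more if sessions or the interview come later.

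The conclusion assumes that the follow-up and exit telephone interviews are the same contact, as the sections read together suggest. It also assumes that the sub-sample mentioned under treatment satisfaction is the group asked about the app. The documents do not support a claim that the interview always falls within the first weeks, or that the study's main conclusions are affected.

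**What to change.** Add two short items for enhanced-arm participants to the 3- and 6-month online surveys already planned:

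1. Are you still using the app, and do you still find it useful?
2. If not, roughly when did you stop, and why?

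Report the answers descriptively, stating how many were still using the app at their last contact, so that incomplete durations are visible. No formal time-to-event analysis is needed. Keep the exit interview for experience of the app during counselling.

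This extends observation to about 6 months from consent and reaches every enhanced-arm participant who responds, rather than a sub-sample. The cost is two extra items in one arm, with no extra contact. The surveys then differ slightly between arms.

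If only usefulness during counselling was meant, a few words saying so in the section on app usage would settle the matter.

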#### Intervention fidelity

Intervention fidelity will be assessed through counselling audio recordings, a focus group with counsellors and telephone interviews with participants. Counselling recordings will be anonymised during transcription and assessed by two reviewers, the onsite researcher (unblinded) and an independent blinded researcher, to permit analysis of inter-rater reliability. A checklist will be provided to score the transcript content which will include the following themes, separately for counsellors and participants: (1) number of times app discussed; (2) duration of app discussion; (3) whether the tablet was used to view app activity; (4) whether there was reason to adjust app usage; (5) whether different app features were advised; and (6) whether there was a missed opportunity to discuss an app feature. Audio recordings will also be assessed against the BACP UCC competency framework to determine clinical competency and to develop the framework for the definitive trial. Finally, intervention fidelity will be assessed in the counsellor focus group and participant interviews to explore challenges of integrating the app with counselling and to provide potential solutions.

#### Client characteristics

Client characteristics will be assessed collectively from (i) intake demographic data, (ii) counsellor notes from the initial clinical assessment, (iii) counsellor session notes and (iv) participant interviews. Combined, this information will be used to develop a client checklist and brief clinical guide to aid decision making on client appropriateness for using a well-being app. This guide is anticipated to inform the inclusion criteria for the definitive trial and will be shared with other UK UCSs interested in offering well-being apps to their students.

#### Therapeutic alliance

Therapeutic alliance will be assessed through the Working Alliance Inventory-Short Form [28] at the end of session 3 of counselling. WAI is a 12-item self-report measure completed separately by the counsellor and their client. Items refer to current views on the counsellor/client and are rated on a 5-point Likert scale (1 = “strongly disagree”; 5 = “strongly agree”) whereby higher scores indicate stronger therapeutic alliance. Items also provide scores on three distinct components of therapeutic alliance including (1) agreement of therapy tasks, (2) agreement of therapeutic goals and (3) presence of an affective bond between clients and counsellors. These therapeutic factors will be compared across the enhanced intervention and TAU conditions to explore differences in therapeutic alliance and inform potential mediators of clinical outcomes to be tested in a definitive trial.

#### Academic coping

To complement the academic distress measure on the CCAPS [17], participants will be asked about their ability to cope academically during follow-up telephone interviews. During the interviews, participants will be asked whether their mental health has affected their studies (or vice versa) and whether they believe that counselling has contributed to their ability to cope academically. These findings will be used to explore the potential contribution UCSs have on academic coping, and will inform outcome assessment for a definitive trial.

### Managing risk and adverse events

All stages of the feasibility trial will take place at the UCS and participants will have immediate access to professional mental health support. Counsellors involved in the trial will also have access to professional mental health support through the duty counsellor in line with standard practice. Efforts have been made to reduce risk in the current study by ensuring that the design, training and delivery of interventions are informed by clinical judgement, and clinical competency is reinforced by the BACP competency framework and UCS clinical handbook. Furthermore, all decisions concerning participant allocation are informed by their assessing counsellor (see “Allocation” section). Counsellor training will also address participant withdrawal and how to report risk. In either event, every individual involved with the trial (e.g. admin, clinical and research) will be informed to report to the duty counsellor allocated at the start of each day. The reporting of adverse events will be recorded through (1) onsite researcher notes throughout trial, (2) therapist clinical notes from triage, (3) therapist notes from counselling and (4) duty therapist clinical notes. In line with the service clinical handbook, adverse events will be reported to the duty therapist and recorded electronically on the service’s secure clinical scheduling system.

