##### Counseling Center Assessment of Psychological Symptoms (CCAPS)

CCAPS [17] is a measure developed in the USA specifically for the student college population and will be administered with CORE-10 at the initial clinical assessment (pre-intervention) and every counselling session to measure changes in student-specific mental health concerns. Items refer to the previous 2-week period and are scored on a 5-point Likert scale (0 = “not at all like me”; 4 = “extremely like me”), whereby higher scores indicate higher symptom severity. In addition, because CCAPS was designed for UCSs to measure student mental health, it also monitors changes in the following areas: depression, generalised anxiety, social anxiety, academic distress, eating concerns, hostility, substance abuse, family distress and suicide ideation. Within each construct, CCAPS determines clinical membership (e.g. clinical versus non-clinical) and severity (e.g. low versus elevated clinical severity), which are detailed in the CCAPS clinical guide. Finally, CCAPS has been validated in UK samples through use in UK UCS and in a recent doctoral research project [18].

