### Data management

A primary researcher (author EB) will be selected to oversee all stages of the feasibility trial and will include the following responsibilities: (1) maintain primary contact with staff at the UCS; (2) deliver counsellor training; (3) deliver research interview with participants; (4) administer and score PHQ-9 and GAD-7 to determine participant eligibility; (5) offer ongoing support to counsellors by maintaining a physical presence at the UCS; (6) offer technical support of computer tablets; and (7) handle trial data from paper and electronic sources. As the primary researcher will oversee all stages of the feasibility trial and will handle all trial data, it was decided not to form a Data Monitoring and Ethics Committee; however, the primary researcher will regularly update with the head of service at the participating trial centre and authors AM and MB as research supervisors for the feasibility trial. Methods of planned data management have been approved by the trial sponsor REC, and have been implemented to be predominantly electronic to avoid human error and optimise data security.

Part of data management will require storing participant consent forms and documents from the research interview in a securely locked filing cabinet at the UCS. The filing cabinet will only be accessed by the primary researcher and the clinical team, if necessary. Therapy audio recordings from computer tablets will be immediately uploaded to an encrypted file (via UCS encrypted Wi-Fi) on the UCS computer system, and will not be stored on computer tablets. This process is automatic and will be triggered when the audio recording app is stopped. Only the primary researcher will have access to the encrypted folder and recordings will be anonymised upon transcription. The remaining sources of clinical data (e.g. from questionnaires) will be administered online via unique survey links emailed to participants. Survey data will only be accessed through a secure account log-in which only the primary researcher will have access to. All data will be backed up on an encrypted external hard drive, accessed only by the primary researcher. Data will be stored in a Microsoft Access database on two encrypted USBs handled by the primary researcher.

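### The safety section places every stage at the counselling service, but follow-up is by emailed survey and telephone, and neither is named as an adverse-event source

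*Protocol article*

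**What the plan says.** All references are to the protocol article.

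- **Premise.** *Managing risk and adverse events* begins: "All stages of the feasibility trial will take place at the UCS and participants will have immediate access to professional mental health support".
- **Adverse-event sources.** The same section lists four: "1) onsite researcher notes throughout trial, (2) therapist clinical notes from triage, (3) therapist notes from counselling and (4) duty therapist clinical notes".
- **Reporting route.** It adds that "every individual involved with the trial (e.g. admin, clinical and research) will be informed to report to the duty counsellor", and that events go onto the service's clinical scheduling system.
- **How questionnaires are collected.** *Data management* says that the remaining clinical data "will be administered online via unique survey links emailed to participants". *Treatment satisfaction* has the CSQ-8 emailed the day after the last session.
- **Who sees the answers.** *Data management*: "Survey data will only be accessed through a secure account log-in which only the primary researcher will have access to".
- **Follow-up contacts.** Table 1 and the sections on the PHQ-9, GAD-7 and CD-RISC 10 schedule these three measures 3 and 6 months after consent. *Treatment satisfaction* and *Academic coping* describe telephone interviews at the end of or after counselling, the former for a sub-sample. Under *Completion rate of follow-up measures*, the stated use of the interviews concerns retention: "telephone interviews will also be used to ask participants how to optimise the follow-up response rate and maintain contact".
- **Risk as an aim.** *Allocation* justifies the use of clinical judgement partly because it helps to monitor risk. *Qualitative analysis* intends an account of the possible risks and benefits of adding the app.

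**The concern.** The first safeguard in the safety section is that everything happens on site, with help at hand. That does not describe follow-up, when participants answer by email link or telephone. The list of adverse-event sources seems to follow the same on-site picture, since it leaves out the scheduled contacts made after counselling ends.

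Risk is one of the things this feasibility trial is meant to report, and a later randomised trial will draw on it. If events after counselling reach the record only by chance, a low count could reflect weak ascertainment and be read as reassurance about the app.

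**Working it through.** No sample size, power or event figure underlies this point, so the check sets the sections side by side.

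**Step 1: is every stage at the service?** The clinical assessment, research interview and counselling sessions are. The telephone interviews and the CSQ-8 emailed after the last session are not tied to the site. The 3- and 6-month measures fall under the emailed-link arrangement in *Data management*, and no on-site visit is scheduled for them. An emailed link could be opened at the service during a session week, but this cannot be assumed once sessions have ended. The opening sentence and the follow-up arrangements therefore do not fit together.

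**Step 2: what does each listed source cover once a participant has finished counselling?**

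| Source | After counselling |
|---|---|
| Onsite researcher notes | Still open; stated to run throughout the trial |
| Triage notes | Belong to the initial assessment, before treatment |
| Counselling notes | Stop for that participant |
| Duty therapist notes | Arise only if someone contacts or reports to the service |

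Of the four, only the researcher's notes could directly pick up something disclosed in a follow-up survey or interview.

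**Step 3: does any section link the follow-up contacts to that source?** The surveys are seen only by the primary researcher. That person is covered by the general instruction to report to the duty counsellor. No section says that survey answers are examined for harm when they arrive, or that interviewees are asked about adverse events. *Data management* states that no monitoring committee was formed, and *Quantitative analysis* starts the analysis only after the 6-month follow-up is complete. Neither of these supplies an earlier look.

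**Result.** The statement about location is contradicted within the article. A path from a late event to the record exists, but it depends on the researcher noticing the event and choosing to note or report it.

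**The case against.** The strongest reply is that a path does exist. Researcher notes have no end date at counselling. The primary researcher oversees all stages, holds the survey account, is present at the service, updates the head of service and supervisors, and falls under the duty to report. The safety section also relies on clinical judgement, competency frameworks, training and the service handbook, so it does not rest on location alone. Exit interviews already feed the account of risks and benefits, and PHQ-9 and GAD-7 at 3 and 6 months would show worsening symptoms at analysis. Finally, an article condenses a fuller protocol, so missing operational detail is weak evidence.

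Most of this stands, and it limits the point to possible under-recording. It does not remove the contradiction, because the opening sentence is a positive statement that other sections of the same article do not support. Nor does it explain why an explicit list of sources omits the scheduled follow-up contacts.

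Four stronger readings are tempting, and the documents do not support them:

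- **That most of follow-up lies outside counselling.** *Counselling interventions* gives 8–10 days between sessions. Six sessions would then span at most 5 × 10 = 50 days and two sessions at least 1 × 8 = 8 days. This would leave 1 − 50/180 = 72% to 1 − 8/180 = 96% of about 180 days. That holds only at this spacing with session 1 at consent. The Abstract allows sessions across 6 months and leaves frequency to client and counsellor, so the share can approach zero.
- **That the CCAPS shows late harms being missed.** It covers "family distress and suicide ideation", but Table 1 ends it at the last session, so it says nothing about 3 or 6 months.
- **That counts by arm will differ because counselling lasts longer in one arm.** Both arms offer up to six 50-minute sessions, and no section suggests a difference in duration.
- **That telephone interviews also sit in the researcher-only account.** The restriction is stated for survey data only.

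**Conclusion.** The point holds in a limited form. The claim that all stages are at the service conflicts with emailed questionnaires and telephone interviews, and the adverse-event list names neither the 3- and 6-month surveys nor the interviews. Events after counselling can be captured, but only incidentally, so they may be under-recorded. A reader might infer that such harms are certain to be lost; the researcher's notes and the reporting duty rule that out.

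No numerical size can be given: the article states no event rates, and the length of counselling is left open. The conclusion assumes that *Data management* covers the 3- and 6-month measures, as its wording indicates, and that the full protocol does not already name these contacts as sources. It is worth correcting because risk is a declared output and the remedy is cheap.

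**What to change.** 1. Correct the opening sentence of *Managing risk and adverse events* and reconcile that section with *Treatment satisfaction*, *Completion rate of follow-up measures* and *Data management*.
2. Add the 3- and 6-month surveys and the telephone interviews to the listed adverse-event sources, in the same way in both arms. State how what they reveal reaches the reporting route the section already sets out, given that only the primary researcher sees survey answers.
3. Report adverse events by arm, separating those during counselling from those after it. Record the source of each event, because the interviews may cover only a sub-sample.

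The clinical response to any disclosure is for the service to decide, and nothing here proposes one.

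The cost is a short amendment and somewhat more review and reporting work for the researcher. No new participant contact is needed.
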